**Background**

Epicondylitis is a common disorder which is difficult to treat, and causes disability in patients and large costs for society. The acute phase is characterized by inflammation in the tendons and their insertions on the lateral epicondylus (5, 7, 8, 9), and anti-inflammatory drugs are adequate and effective.

In chronic epicondylitis (symptoms for more than 3 months) inflammation is usually absent while degeneration predominates (9, 11, 12). The cause of pain is mainly unclear. Recent research on chronic epicondylitis, and particularly on similar disorders in tendons of the shoulder and the heel, suggests ingrowth of peripheral nerves. Both nerve fibers and neuro-peptides have been found in the affected tissue (1, 3, 4, 6). It is therefore of no surprise that anti-inflammatory drugs have little to offer in this stage. Unfortunately other treatments with proven effect are also lacking, although many have been suggested. Promising results have, however, recently been reported from training programs with increasing load on tendons and their insertions during the eccentric phase (lengthening) of muscle contraction (2, 10, 13).

This is a randomized clinical trial in patients with chronic epicondylitis to investigate the involvement of the peripheral nervous system and to evaluate the effects of eccentric exercise in comparison with concentric exercise (muscle shortening). This trial provides a unique opportunity to investigate the role of peripheral nerves in chronic epicondylitis, and the possible influence of two different training methods. The involvement of peripheral nerves in the disease process can be examined using positron-emission-tomography (PET) or histochemical analyses of biopsies. If both methods are used the information provided can be compared. The role of peripheral nerves will be studied in a subsample of patients. Healthy volunteers will be examined accordingly.

Approvals from the Regional Ethics Committee in Uppsala and the Radiation Safety Committee in Uppsala have been obtained for for both tracers GLD and D-Deprenyl.

Informed consent will be obtained from all patients and healthy volunteers. Patient data registration has been approved according to the present law (”Personuppgiftslagen”).

**Main trial**

Aim:

To evaluate the effect of eccentric excercise in comparison with concentric excercise on pain, strength and activities of daily life (ADL) in patients with chronic epicondylitis.

Methods:

Two hundred (200) patients with chronic epicondylitis will be randomized to either eccentric or concentric excercise for three months. Pain and strength will be registered before start of treatment and after 1,2,3,6 and 12 months. Activities of daily life and well-being will be examined using questionnaires (DASH and Gothenburg Quality of Life) before start of treatment and after 3,6 and 12 months. Patient data will be registered in specially designed case record forms. Results will be analyzed using analysis of variance and logistic regression.

Inclusion Criteria:

- Verified tennis elbow for more than three months
- Age 20-75 years
- Informed consent

Exclusion Criteria:

- Inability to understand or follow instructions
- Inability to read or fill in questionnaires
- Inability to participate at measurement sessions
- Supinator syndrome
- Compartment syndrome of anconeus muscle
- Rhizopathy of arm
- Inflammatory joint or soft tissue disease including fibromyalgia
- Previous surgery because of tennis elbow

Randomization and blinding

Patients are consecutively distributed in blocks of four to the two exercise groups by the aid of a computergenerated randomizationlist.

Training and evaluation of pain and ADL cannot be blinded but all handling of data will be blinded.

Tissue samples will be ananymous and coded during analysis.

Analysis of positron emission tomography (PET) images will be blinded to the analyzer.

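### Analysis of variance is named for outcomes that all have a baseline value, with no baseline covariate; each usual form of it is less precise than a baseline-adjusted analysis

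*Protocol*

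**What the plan says.** The Methods paragraph under Main trial in the Protocol gives the design: "Two hundred (200) patients with chronic epicondylitis will be randomized to either eccentric or concentric excercise for three months". The paragraph on randomization adds: "Patients are consecutively distributed in blocks of four to the two exercise groups". Two groups in blocks of four imply 1:1 allocation, so about 100 patients per arm.

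On measurement: "Pain and strength will be registered before start of treatment and after 1,2,3,6 and 12 months". That is a baseline and five follow-up visits. DASH and the Gothenburg Quality of Life questionnaire are completed "before start of treatment and after 3,6 and 12 months", a baseline and three follow-up visits.

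On analysis, the section has one sentence: "Results will be analyzed using analysis of variance and logistic regression". It does not say whether the dependent variable is the follow-up value or the change from baseline, how the visits enter, or what happens when a visit is missed. Baseline is not named as a covariate, and it is not ruled out either.

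**The concern.** The protocol schedules a baseline value for every main-trial outcome and then names a method family that, in its usual forms, either ignores that value or uses it inefficiently. Comparing follow-up values alone ignores it. Subtracting it forces a slope of 1, which adds noise when the correlation is modest. Treating it as one more occasion in a repeated-measures analysis averages the arm difference over an occasion at which treatment cannot yet have had an effect.

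What is at stake is precision, and in the follow-up-only form also exposure to chance baseline imbalance. Randomization keeps the comparison valid with complete data, so this is not a flaw that invalidates the trial. It is information already paid for and not fully used. A further risk, the loss of whole patients after one missed visit, arises under only one of the possible forms.

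**Working it through.** **Inputs from the Protocol (Main trial).** 200 patients, about 100 per arm; five follow-up visits for pain and strength; three for DASH and quality of life.

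**Assumptions.** The protocol gives no alpha, power, effect size, SD, correlation or rate of missed visits, so it has no sample-size figure to reproduce. I assume two-sided alpha of 0.05, an effect of 0.40 SD, equal variance at all visits (set to 1), a baseline-to-follow-up correlation r of 0.3, 0.5 or 0.7, and 5% or 10% of patients missing at each visit. The effect of 0.40 SD is close to what a follow-up-only comparison of this size detects with 80% power: (1.960 + 0.842) × √(2/100) = 0.396 SD.

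**Step 1: one follow-up visit.** Relative variance of the arm difference:
- follow-up value only: 1
- change score: 2(1 − r)
- adjusted for baseline: 1 − r²

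| r | Change score | Adjusted | Adjusted ÷ follow-up only | Adjusted ÷ change |
|---|---|---|---|---|
| 0.3 | 1.40 | 0.91 | 0.91 | 0.65 |
| 0.5 | 1.00 | 0.75 | 0.75 | 0.75 |
| 0.7 | 0.60 | 0.51 | 0.51 | 0.85 |

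The last column equals (1 + r)/2, which is below 1 for every r below 1. Adjustment therefore beats the change score throughout the range. At r = 0.3 the change score is worse than ignoring baseline (1.40 against 1).

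**Step 2: power at 0.40 SD, 100 per arm (two-sample t-test).**

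| r | Follow-up only | Change score | Adjusted |
|---|---|---|---|
| 0.3 | 80% | 66% | 84% |
| 0.5 | 80% | 80% | 90% |
| 0.7 | 80% | 95% | 98% |

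**Step 3: repeated measures with baseline as one of six occasions (pain, strength).** Assume the same correlation r between any two occasions and a constant effect after baseline. The group main effect is then 5/6 of the true effect, with variance (1 + 5r)/6. Rescaled to the full effect, the variance is (36/25) × (1 + 5r)/6. The baseline-adjusted mean of the five follow-up visits has variance (1 + 4r)/5 − r².

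| r | Group main effect, rescaled | Adjusted five-visit mean | Ratio | Power, main effect | Power, adjusted |
|---|---|---|---|---|---|
| 0.3 | 0.60 | 0.35 | 0.58 | 95% | >99% |
| 0.5 | 0.84 | 0.35 | 0.42 | 87% | >99% |
| 0.7 | 1.08 | 0.27 | 0.25 | 77% | >99% |

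These powers are higher than in Step 2 because five visits are averaged. The comparison to make is within each row.

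**Step 4: missed visits, only if complete data are required.** With independent missingness q at each of k follow-up visits, the share dropped is 1 − (1 − q)^k.
- Pain and strength, k = 5: 1 − 0.95⁵ = 23% (about 45 of 200); 1 − 0.90⁵ = 41% (about 82 of 200).
- DASH and quality of life, k = 3: 1 − 0.95³ = 14% (about 29 of 200); 1 − 0.90³ = 27% (about 54 of 200).

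**The case against.** The strongest objection is that the sentence names method families and nothing more. A reader might infer that the protocol has fixed an analysis that leaves baseline out. The text does not support that: it is silent on baseline, and covariates are often settled in a SAP, which is not at hand. This limits the claim. It does not remove it, because the protocol does choose a method, and Steps 1 to 3 show that the choice is less precise under each usual form.

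A reader might also infer that the stated analysis both wastes precision and discards patients who miss a visit. The two losses belong to different forms and must not be added. The ratio 1 − r² is measured against a follow-up-only analysis. Dropping whole patients needs a complete-case repeated-measures analysis, which the protocol nowhere specifies. A separate analysis at each visit loses a patient only at the visit missed.

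The percentages in Step 4 also depend on missed visits being independent. If patients mostly leave for good, the complete-case loss is just the final dropout rate and does not compound. It would be tempting to turn the reduced numbers into a power figure with a two-sample t-test, but that would not be the power of the repeated-measures analysis in question, so none is given.

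Finally, every figure for r, the effect and the missed visits is assumed. The sizes are therefore illustrative. The direction holds for any r between 0 and 1.

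**Conclusion.** The point holds as a matter of efficiency. The protocol names analysis of variance for outcomes with a scheduled baseline and does not name that baseline as a covariate. Against a follow-up-only analysis, adjustment cuts the variance by 9% to 49% for r from 0.3 to 0.7. Against a change score it cuts it by 35% down to 15% over the same range. The gain over the group main effect of a repeated-measures analysis is larger, under the equal-correlation and constant-effect assumptions of Step 3.

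The loss of whole patients is conditional on a form of analysis that the protocol does not state, and on independent missingness. It is a reason to word the method clearly and should not be charged to the plan as written. The change is worth making because it costs almost nothing. Without it, the results of a randomized comparison would still be valid when data are complete.

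**What to change.** In the analysis sentence under Main trial, Methods, replace analysis of variance for the continuous outcomes with: *analysis of covariance adjusting for the baseline value of the outcome, fitted across visits as a mixed model that uses all observed post-baseline visits of all randomised patients in their allocated arm*. Keep logistic regression for binary outcomes.

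The protocol names no main time point. This wording does not settle that; the model gives an arm difference at every visit. The covariance structure can be left to the SAP.

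The cost is a change of wording before the data are analysed. The baseline values are already scheduled, so no extra patients, visits or measurements are needed.

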**Substudy on peripheral nerve involvement**

Aims:

1) To assess the involvement of peripheral nerves in the tendons of the lateral epicondylus in patients with chronic epicondylitis using PET and histochemical analyses of biopsies.

2) To evaluate and compare the effect of eccentric and concentric excercise on peripheral nerves in the tendons of the lateral epicondylus in patients with chronic epicondylitis, using PET and histochemical analyses of biopsies.

Methods:

Ten patients from each treatment group (twenty in total) and ten healthy volunteers will be examined for:

1) Substance P-receptors using PET after intravenous injection of a C-marked selective NK-receptor antagonist 2 - metoxy - 5 - (5 - trifluorometyl -tetrazol -1- yl) - bensyl -(2S - fenyl - piperidin - 3S - yl) - amin (reference number GR-20 51 71, GLD).

2) Inflammation using (N-methyl-11-C)-D-deprenyl, DDE.

The patients will be examined before start of treatment and after three months. The healthy volunteers will only be examined once.

Signal intensity in both the healthy and the painful elbow will be analyzed. Half life of radioactive ligand is about 20 minutes and after approximately 2 hours the radiation will end. Total dose of radiation is 6,4 mSv equivalent to 3 years background radiation.

From 20 patients from each treatment group (40 in total) and 20 healthy volunteers a biopsy will be taken from the tendon at its insertion on the lateral epicondylus. This sample will be examined for nerve fibers and neuro-peptides using immuno-histochemistry and radioimmunoassay (RIA). Biopsies will be taken before start of treatment and after three months from the patients, but only once from the volunteers.

Patient data will be registered in specially designed case record forms. Results will be analysed using analysis of variance and logistic regression.

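### Substudy Aim 2: adjusting the 3-month arm comparison for the baseline scan or biopsy would be more precise than either natural form of the stated analysis of variance

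*Protocol*

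**What the plan says.** All of this is in the protocol section on the substudy of peripheral nerve involvement.

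- **Aim 2** is comparative: "To evaluate and compare the effect of eccentric and concentric excercise on peripheral nerves in the tendons".
- **PET sample:** "Ten patients from each treatment group (twenty in total) and ten healthy volunteers will be examined for" two tracer targets. On timing: "The patients will be examined before start of treatment and after three months". For volunteers: "The healthy volunteers will only be examined once".
- **PET elbows:** "Signal intensity in both the healthy and the painful elbow will be analyzed".
- **Biopsy sample:** "From 20 patients from each treatment group (40 in total) and 20 healthy volunteers a biopsy will be taken from the tendon". On timing: "Biopsies will be taken before start of treatment and after three months from the patients, but only once from the volunteers". No second elbow is mentioned for biopsies.
- **Analysis:** "Results will be analysed using analysis of variance and logistic regression". This is the only analysis statement for the substudy. It does not mention the baseline value, the pairing of elbows or the unit of analysis.

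**The concern.** Aim 2 is a randomised comparison in very small groups, and every patient in it has a pre-treatment value of the same measure. That value can remove part of the between-patient variation from the 3-month comparison. The method named does not obviously do this well.

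Read as a one-way comparison at 3 months, analysis of variance leaves the baseline unused. Read as a two-visit repeated-measures analysis, its test of a differential training effect is the arm-by-visit term, which equals a two-sample comparison of changes. That uses the baseline with a fixed slope of 1, which is too steep unless the correlation between visits is close to 1.

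What is at stake is precision. With 10 or 20 patients per arm only large effects are detectable, and each patient undergoes two scans or two biopsies. No bias or excess of false positives follows from either form.

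**Working it through.** **Inputs from the protocol.** Patients per arm: 10 (PET) and 20 (biopsy). Visits per patient: 2. The substudy states no power, significance level, effect size, SD or correlation, so there is no planned figure to reproduce.

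**Assumptions.** Two-sided 5% level, 80% power, the same SD at both visits (taken as 1), no dropout, and baseline-to-3-month correlation ρ of 0.3, 0.5 or 0.7.

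**Variance of the arm difference, relative to 3-month values only**

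- 3-month values only: 1, with 2n − 2 df.
- Change, or the arm-by-visit term: 2(1 − ρ), with 2n − 2 df. This gives 1.4 / 1.0 / 0.6.
- ANCOVA on baseline: 1 − ρ², with 2n − 3 df. This gives 0.91 / 0.75 / 0.51.

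The ordering does not depend on the choice of ρ. For any ρ other than 0, 1 − ρ² is below 1. The ratio of ANCOVA to change is (1 − ρ²) / [2(1 − ρ)] = (1 + ρ)/2, which is below 1 for any ρ below 1. Only the lost degree of freedom, and the chance-imbalance term at the end, work against ANCOVA.

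**Detectable difference.** Solve the noncentral-t power equation, with noncentrality d / √(2v/n) and v the factor above, for 80% power. With v = 1 this gives:

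- n = 10: 1.325 SD with 18 df, and 1.330 SD with 17 df.
- n = 20: 0.909 SD with 38 df, and 0.910 SD with 37 df.

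Multiply by √v. For PET change at ρ = 0.3, 1.325 × √1.4 = 1.57. For PET ANCOVA at ρ = 0.3, 1.330 × √0.91 = 1.27. For biopsy ANCOVA at ρ = 0.7, 0.910 × √0.51 = 0.65.

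| Detectable difference (SD) | ρ = 0.3 | ρ = 0.5 | ρ = 0.7 |
|---|---|---|---|
| PET, 3-month only | 1.32 | 1.32 | 1.32 |
| PET, change | 1.57 | 1.32 | 1.03 |
| PET, ANCOVA | 1.27 | 1.15 | 0.95 |
| Biopsy, 3-month only | 0.91 | 0.91 | 0.91 |
| Biopsy, change | 1.08 | 0.91 | 0.70 |
| Biopsy, ANCOVA | 0.87 | 0.79 | 0.65 |

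**The same result as power.** For a true difference of 1 SD with 10 per arm, power is 0.56 for 3-month values, 0.43 / 0.56 / 0.78 for change and 0.60 / 0.68 / 0.84 for ANCOVA.

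**Sensitivity.** The ANCOVA factor ignores chance imbalance in baseline between arms. Allowing for it multiplies the detectable difference by about √(1 + 1/(2n − 4)). That is √(1 + 1/16) = 1.031 for PET and √(1 + 1/36) = 1.014 for biopsies. ANCOVA then becomes about 1.31 / 1.19 / 0.98 SD and 0.88 / 0.80 / 0.66 SD. It remains the best of the three in every column, but for PET at ρ = 0.3 its lead over 3-month values almost disappears.

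**The case against.** The strongest reply is that the protocol sentence names a family of methods and fixes no model. Covariates and error structure are usually left to a statistical analysis plan, which may exist and is not shown. Repeated-measures analysis of variance belongs to the named family and uses both visits, and some would count ANCOVA in it too. The gain also depends on a correlation that nobody has stated.

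Much of this stands. The sentence contains no demonstrated error, and a plan that already specifies ANCOVA would settle the matter. What the reply does not remove is the comparison itself. The two forms that the sentence most naturally suggests are each less precise than ANCOVA at all three assumed correlations, and repeated measures does not rescue Aim 2: at 0.3 it is worse than leaving the baseline out.

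Three stronger readings are tempting, and the text supports none of them.

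- **Independent rows.** A reader might infer that elbows and visits will be analysed as independent observations, which would distort error rates. The protocol does not say so. Inflation would need pre-treatment and healthy-elbow values to be pooled into the arm comparison, a test that the section does not describe and that would not answer Aim 2.
- **Logistic regression.** A reader might infer that PET signal or neuropeptide levels will be dichotomised. Logistic regression is named, but it is not assigned to any outcome and no cut-point is given.
- **Two elbows in both parts.** A reader might carry the paired-elbow structure over to the biopsy arms of 20. The protocol gives two elbows for PET only; the biopsies have before-and-after pairing alone.

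**Conclusion.** The point holds as a free improvement to Aim 2. It is not an error that threatens validity: leaving out the baseline in a randomised comparison costs precision and does not disturb type I error.

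The size depends on the correlation. At 0.5, ANCOVA lowers the detectable difference from 1.32 to 1.15 SD for PET and from 0.91 to 0.79 SD for biopsies, against either alternative. At 0.7 the gain over 3-month values is large (1.32 to 0.95 SD and 0.91 to 0.65 SD), and the gain over change is modest (1.03 to 0.95 SD and 0.70 to 0.65 SD). At 0.3 the gain over 3-month values is small, and for PET close to nil once chance imbalance is allowed for, but the gain over change is large (1.57 to 1.27 SD and 1.08 to 0.87 SD). So ANCOVA is the safe choice when the correlation is unknown.

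These figures rest on the assumed correlations, equal SDs at the two visits, complete data, 80% power and a two-sided 5% level. For the Aim 1 elbow contrast only a clarification is due, since the text does not say that pairing is ignored.

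**What to change.** In the substudy analysis statement, or in the statistical analysis plan if one exists:

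1. **Aim 2.** Compare the arms on the 3-month painful-elbow PET signal (for each tracer) and on the 3-month biopsy measure, both kept continuous, by analysis of covariance with the same patient's baseline value as covariate. A mixed model with an arm-by-visit term is no substitute: with complete two-visit data and the usual arm main effect it is the change-score test again.
2. **Aim 1, PET elbow contrast.** State that the within-patient painful-minus-healthy difference is analysed, with the patient as the unit.

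The cost is a change of wording and one degree of freedom (17 instead of 18 for PET, 37 instead of 38 for biopsies). No further scan, biopsy or patient is needed, because the baseline values are already scheduled.

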**Importance of the study**

Chronic pain from tendons and their insertions is a common problem that causes disability in patients and great costs for society. Lack of understanding of the mechanisms behind the pain can partly explain the fact that effective treaments are missing. It is conceivable that better understanding of the pathology in these conditions can contribute to improved treatments.

This study provides the opportunity to further evaluate the possible involvement of the periheral nervous system in the pain process in chronic epicondylits. It will also allow the investigation of the efficiency and mechanisms of different types of training.

